
The benefit of coordinated primary care, in terms of the beliefs, feelings, and satisfaction of patients and healthcare professionals will also be assessed using the following secondary outcome measures:

The changes in the occupational and physical scores of the Fear Avoidance Beliefs Questionnaire (FABQ). The self-administered FABQ evaluates the patient’s fears and beliefs surrounding LBP (29). The validated French version of the FABQ was used during the study (30). The FABQ comprises 16 items divided into two dimensions: the physical (items 1–6) and the occupational (items 7–16). Each item is scored from “0” (completely disagree with the statement) to “6” (completely agree with the statement). Thus, the maximum score is 36 for the physical dimension and 60 for the occupational dimension. The FABQ will be completed by patients at baseline, and at 3 and 12 months.The change in the Patient-Centered Coordination by a Care Team (PCCCT) questionnaire. The PCCCT instrument measures the quality of primary care from the patient’s perspective. The questionnaire is composed of 14 items each scored from 0 to 3 (31). The overall score will range from 0 (worst coordination) to 42 (best coordination). The PCCCT questionnaire will be completed by patients at baseline and at 3 and 12 months.The change in the GPs’ satisfaction with the healthcare provided for their patients’ LBP.The change in the physiotherapists’ satisfaction (only in the Coordinated-care group) with the healthcare provided for their patients’ LBP.

The GPs’ and physiotherapists’ satisfaction will be measured, on a scale from 0 (not satisfied) to 10 (completely satisfied), at the following timepoints: when the cluster is initiated, at 6 months after the 5th patient is included in each cluster, and at the end of the follow up of the last patient in each cluster. The GPs’ satisfaction will be compared between the study groups.

The level of implementation of coordinated primary care (the study intervention) will be assessed using the following secondary outcome measures:

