### Sample size

To calculate the sample size required for the study we hypothesize that 50% of patients in the control group (Usual-care group) and 70% of those in the interventional group (Coordinated-care group) will have a significantly reduced disability at 12 months after being enrolled (3, 33). Considering a cluster randomized study with the following statistical characteristics:

A power of 80%.A type 1 error (α-risk) of 0.05.A mean cluster size of 25 patients.A coefficient of variation in the cluster size of 0.2.An intraclass correlation coefficient of 0.03.An attrition rate of 20%.

To show a difference of 20% between the study groups (70% vs. 50%) the study needs to include 10 clusters of 25 patients in each study group. Therefore, a total of 20 clusters of 25 patients: 500 patients are required for the study. The sample size was calculated using Stata (Stata 13.1 software, package clustersamplsi).

This sample size is realistic considering that GPs on average perform 2,500 consultations per year in patients aged between 18 and 60 years (34). Among these 1 of every 200 consultations concerns subacute LBP (35). Therefore, on average 12–13 patients per year with subacute LBP consult each GP in France. The number of consultations for recurrent acute LBP is more difficult to estimate but is about as frequent as those for subacute LBP. The planned patient enrollment period is 24 months for any given cluster. Each cluster will consist of at least 4 GPs. Therefore, the study target of recruiting 25 patients per cluster is feasible. The total planned enrollment period is 36 months, comprising an initial 12-month period during which the clusters will be initiated followed by a 24-month patient enrollment period.

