### Statistics

Quantitative data will be presented as means with standard deviations and will be compared using Mann–Whitney tests. Qualitative data will be presented as numbers with percentages and compared using Fisher’s exact tests.

For the primary objective, the proportion of patients that have an improved (lower score) of at least 4 points, in the RMDQ, at 12 months after enrollment will be compared in the study groups. The analysis will be performed using a multilevel logistic mixed model that will allow the clustering effect to be considered as random.

Similarly, the secondary outcome measures with binary outcomes compared between the study groups (e.g., the proportion of patients that improved by at least 2 points on the numerical pain scale at 12 months) will be analyzed by multilevel logistic mixed regression models.

Secondary outcome measures assessing changes in a quantitative parameter over time (e.g., the evolution of the RMDQ scores measured at baseline and then at 3, 6, and 12 months after enrollment) will be analyzed using linear multilevel mixed regression models. The individual effect will be included in the cluster effect. Time will be considered as qualitative variables with a varying number of modalities, e.g., 4 modalities for outcomes assessed at baseline, and then at 3, 6, and 12 months, and 3 modalities for outcomes assessed at baseline, and then at 3 and 6 months. The effect of the intervention will be evaluated by including an interaction between the variables for time and for the study group. The effect of the intervention will be assessed at each time point. The increased alpha-risk, due to multiple analyses, will be accounted for using the Bonferroni correction.

For these various multilevel models, the variance–covariance matrices will be considered as unstructured. Missing data will be treated using a set of 10 multiple imputations based on chained equations (38, 39). The analyses will be performed bilaterally with the alpha-risk set at 5%, except in cases where the Bonferroni correction was used. The data will be analyzed on an intent-to-treat basis. Thus, all patients with data will be included in the analysis unless they specifically indicate that they do not want their data analyzed.

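### The mixed models for continuous secondary outcomes name no cluster-by-time effect, so between-cluster variation in change may be left out of the standard errors; the three-level time factor also matches no outcome's visits

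*Protocol article*

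**What the plan says.** The Statistics section assigns quantitative outcomes followed over time to linear multilevel mixed models. On the random effects it says: "The individual effect will be included in the cluster effect". Time is categorical and baseline is one of its levels. The treatment effect is defined by this sentence: "The effect of the intervention will be evaluated by including an interaction between the variables for time and for the study group". The effect is read at each time point, with a Bonferroni correction for multiple analyses. A later sentence makes the variance-covariance matrices of all the multilevel models unstructured, without saying at which level (cluster, patient or residual). No cluster-by-time effect is mentioned.

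The section gives two examples of the time factor. The four-level one (baseline, 3, 6 and 12 months) agrees with the schedule for RMDQ, pain and SF-12. The other reads: "3 modalities for outcomes assessed at baseline, and then at 3 and 6 months". Under Secondary objectives and outcomes, however: "The FABQ will be completed by patients at baseline, and at 3 and 12 months". The same section and Table 1 give that schedule for HADS and PCCCT as well.

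**The concern.** The trial randomizes 20 clusters, so the standard error of any treatment contrast should carry the variation between clusters in the quantity being compared. Here that quantity is change from baseline. A cluster effect that is the same at every visit adds equally to the baseline and follow-up scores and disappears when one is subtracted from the other. The model then holds a cluster effect, but none of it reaches the tested contrast. If clusters differ in how much their patients change, that variation is missing from the standard error.

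At stake are the p-values and intervals for RMDQ and pain evolution, SF-12, HADS, FABQ and PCCCT. The visit mismatch is a second, smaller matter: read literally, the three-level model has no place for the 12-month FABQ, HADS and PCCCT data.

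**Working it through.** **Inputs from the documents.** Twenty clusters, 10 per arm (Randomization). From Sample size: "A mean cluster size of 25 patients", ICC 0.03, coefficient of variation of cluster size 0.2, attrition 20%, and a cited median ICC of 0.01 with interquartile range 0 to 0.032. After attrition, 25 × 0.8 = 20 patients per cluster.

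**The plan's own figure.** The design effect is 1 + ((1 + 0.2²) × 25 − 1) × 0.03 = 1.75. For 70% against 50%, two-sided 5%, with a t reference on 2k − 2 degrees of freedom, k = 7 clusters per arm give about 77% power and k = 8 about 83%. Eight clusters are 200 patients; 200/0.8 = 250 per arm, or 10 clusters of 25, 500 in total. The stated 500 reproduces, and nothing below alters it. The plan gives no figure for the longitudinal models.

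**Assumptions not in the documents.** Half of the within-cluster variance is stable within a patient (correlation 0.5). The correlation *c* of cluster effects between two visits is varied from 1 to 0.

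**Variance of the contrast.** With total variance 1 at each visit:

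- cluster-level variance of change: τ = 2 × ICC × (1 − c)
- patient-level variance of change: e = 2 × (1 − ICC) × (1 − 0.5) = 1 − ICC
- true variance of a cluster's mean change: τ + e/m
- variance used by the model if the cluster effect is a constant intercept: (τ + e)/m
- ratio R = (mτ + e)/(τ + e); true error of a nominal 5% test = 2 × (1 − Φ(1.96/√R))

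Example with ICC 0.03, m = 20, c = 0.5: τ = 0.03, e = 0.97, R = (0.60 + 0.97)/1.00 = 1.57, error 11.8%.

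| c | ICC 0.03, m = 20 | ICC 0.03, m = 25 | ICC 0.01, m = 25 |
|---|---|---|---|
| 1 | R 1.00, 5.0% | R 1.00, 5.0% | R 1.00, 5.0% |
| 0.8 | R 1.23, 7.7% | R 1.29, 8.5% | R 1.10, 6.1% |
| 0.5 | R 1.57, 11.8% | R 1.72, 13.5% | R 1.24, 7.8% |
| 0 | R 2.11, 17.7% | R 2.40, 20.6% | R 1.48, 10.7% |

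Simulation of 20 clusters and four visits (10,000 runs per cell) agrees. For c = 1, 0.8, 0.5 and 0 it gives 4.6%, 7.5%, 12.1%, 17.9% in the first column; 4.9%, 8.5%, 13.2%, 20.3% in the second; 5.1%, 6.3%, 8.2%, 10.8% in the third. A t-test on cluster mean changes (18 degrees of freedom), which keeps the cluster variation, stays between 4.7% and 5.2%.

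**Bonferroni.** At an assumed 0.05/3 = 1.67% per test (ICC 0.03, m = 25), the simulated error is 3.3%, 6.6% and 12.1% for c = 0.8, 0.5 and 0, and 1.5% for c = 1. The threshold falls, but the relative inflation remains.

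**The unstructured matrix, by level.** At patient or residual level it describes how one patient's visits correlate. Patients in a cluster are still treated as independent in their changes, so R is as above. At cluster level, over four time effects, nothing cancels, but 4 × 5/2 = 10 variance parameters must be estimated from 20 clusters.

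**Visits side by side.** Statistics, three-level case: baseline, 3, 6 months. FABQ, HADS, PCCCT: baseline, 3, 12 months. GP and physiotherapist instruments: cluster initiation, 6 months after the fifth patient, end of follow-up. No outcome has the first schedule.

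**The case against.** A reader might infer that p-values for these outcomes will be too small. The documents do not support that. The article nowhere says that the cluster effect is only a constant intercept. An unstructured matrix has no content for a single intercept per level, so the sentence must refer either to several random effects or to residuals. If it refers to time effects at cluster level, the standard errors are not understated; the problem becomes one of estimation. A journal article may also leave the exact random-effects specification to a fuller document. These points stand and make the finding conditional.

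Inflation also needs cluster means to drift between visits, and the article gives no correlation for that. Zero is an extreme, and the plan itself calls ICC 0.03 conservative. Some drift is nevertheless plausible. The primary outcome is itself an improvement from baseline, and the plan gives it an ICC of 0.03. As a rough translation to continuous change, the c = 0.5 row implies exactly that: τ/(τ + e) = 0.03/(0.03 + 0.97) = 0.03. Clusters also choose their own ways of collaborating and adapt the letter templates locally.

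A reader might further infer that a group-by-time test with baseline as a level is itself invalid. It is a standard analysis; what is missing is the cluster-by-time term. Finally, the three-level case is introduced as an example and the schedule is consistent everywhere else, so it is probably a slip and not a decision to drop 12-month data.

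**Conclusion.** The concern holds conditionally. The text does not secure a cluster-level effect on change. If the cluster effect is a constant intercept, including when *unstructured* refers only to the patient or residual level, p-values can be too small. The true error of a nominal 5% test is then about 8% to 20% at ICC 0.03 (20 to 25 per cluster) and about 6% to 11% at ICC 0.01 (25 per cluster), for assumed between-visit cluster correlations of 0.8 down to 0 and within-patient correlation 0.5. It is about nominal if cluster effects do not change. Under the cluster-level reading there is no cancellation, but the matrix may be hard to estimate.

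The visit mismatch is a plain contradiction, whatever its cause.

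Only continuous secondary outcomes are touched. The primary analysis compares a proportion at 12 months in a logistic model with a random cluster effect, where nothing cancels.

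**What to change.** For RMDQ, pain, SF-12, HADS, FABQ and PCCCT, model the follow-up scores with the baseline score as a covariate, group-by-visit fixed effects, random cluster and cluster-by-visit effects, and an unstructured within-patient residual. Read the group difference at each visit. State the level to which *unstructured* applies.

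The cluster-by-visit effect protects the standard errors. The baseline covariate is an efficiency gain, not the correction of an error: relative to change scores the patient-level variance ratio is (1 + r)/2, so the variance falls by 20% at an assumed r = 0.6 (1 − 0.80) and 35% at r = 0.3 (1 − 0.65). Baseline scores are already collected.

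In the Statistics section, change the three-level time factor to baseline, 3 and 12 months.

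The cost is wording and one extra variance component, with possible convergence difficulty with 20 clusters. No new data and no change in sample size are needed.

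### With 20 clusters, the primary test has no stated small-sample reference and the imputation no stated cluster term; run in ordinary form, its type I error is about 7% to 8%, not 5%

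*Protocol article*

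**What the plan says.** For the primary outcome (a fall of at least 4 points on the RMDQ at 12 months), the protocol article, Statistics, states: "The analysis will be performed using a multilevel logistic mixed model that will allow the clustering effect to be considered as random". On missing values it says: "Missing data will be treated using a set of 10 multiple imputations based on chained equations". On the level of the test it says: "The analyses will be performed bilaterally with the alpha-risk set at 5"%, with an exception only where Bonferroni applies.

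The Sample size section sets the scale: "a total of 20 clusters of 25 patients: 500 patients are required for the study". It also assumes "An attrition rate of 20"%, an ICC of 0.03, and 50% against 70% responders.

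The same Statistics text settles the number of imputations, the covariance structure, sidedness, alpha and the multiplicity rule. It gives neither a reference distribution or degrees of freedom for the primary test, nor the variables and levels of the imputation model.

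**The concern.** Two features of the plan can each push the primary test above its stated level.

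- **Few clusters.** The arm effect is a between-cluster comparison, so 20 clusters carry about 18 degrees of freedom, however many patients there are. A Wald z-test treats the standard error as known, and maximum likelihood also tends to underestimate the between-cluster variance with so few clusters.
- **Imputation without cluster.** If missing 12-month outcomes are drawn as though patients in a cluster were independent, the completed data show less between-cluster variation than is real. Rubin's rules restore the patient-level uncertainty but not the lost cluster component.

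At stake are the 5% level of the single primary test and the width of its confidence interval. The method as written can be carried out literally in this form, and nothing in the text prevents it.

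**Working it through.** **Inputs (Sample size and Statistics sections).** Two-sided alpha 0.05; power 80%; 50% v 70%; 10 clusters of 25 per arm; ICC 0.03; coefficient of variation (CV) of cluster size 0.2; attrition 20%; M = 10 imputations. The Sample size section also gives the CV as 0.02. I use 0.2 because it reproduces the stated size.

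**1. The planned size.** Two proportions at 50% v 70% need 93 per arm, or 103 with continuity correction.
- Design effect = 1 + ((1 + CV²)m − 1) × ICC = 1 + (1.04 × 25 − 1) × 0.03 = 1.75.
- 103 × 1.75 = 180.2; divided by 0.8 = 225.3; divided by 25 = 9.01, hence 10 clusters per arm and 500 patients. The plan's figure is reproduced.
- With CV 0.02 the result is 8.86, hence 9 clusters.

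**2. Few clusters alone.** If the statistic follows t with 18 df (20 clusters minus 2 arm means), P(|t| > 1.96) = 6.6%. With three region terms (15 df) it is 6.9%.

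Simulation under the null: 20 clusters, mean size 25, CV 0.2, response 50%, ICC 0.03, 5,000 runs, random-intercept logistic model by quadrature.
- No missing data: Wald z rejects 7.3%; t with 18 df rejects 5.6%.
- 20% missing, observed data only: Wald z 7.1%; t with 18 df 5.2%; model SE 0.967 of the true SD.

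**3. Imputation that ignores cluster, analytically.** Take an arm mean with equal clusters, m = 25 enrolled, 20 observed, missing fraction d = 0.2, in units of patient variance divided by number of clusters.
- Within-imputation variance: (1/25)(1 + 24 × 0.8² × 0.03) = 0.0584. The factor 0.8² is the share of within-cluster pairs in which both values are real.
- Between-imputation variance B: 0.2² × (1/20) + 0.2 × (1/25) = 0.002 + 0.008 = 0.010.
- Rubin total: 0.0584 + 1.1 × 0.010 = 0.0694.
- True variance of the pooled mean: (1/20)(1 + 19 × 0.03) + 0.010/10 = 0.0785 + 0.001 = 0.0795.
- SE ratio: √(0.0694/0.0795) = 0.935, so the imputation alone takes off about 6%. The ratio is 0.972 at ICC 0.01.

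**4. Both together.** Multiplying the two ratios gives 0.935 × 0.967 = 0.904. Simulation with arm-only, single-level imputation and Rubin's rules (missing at random within arm) gives:

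| ICC | Missing | SE/true SD | Rejection, Rubin df | Rejection, t with 18 df |
|---|---|---|---|---|
| 0.01 | 20% | 0.956 | 5.9% | 4.7% |
| 0.03 | 10% | 0.932 | 7.5% | 5.6% |
| 0.03 | 20% | 0.910 | 8.1% | 6.3% |
| 0.03 | 30% | 0.893 | 7.9% | 6.3% |

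A further simulation at ICC 0.03 and 20% missing put the ratio at about 0.92 with rejection again about 8%. Monte Carlo error is about 0.4 points.

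**5. Power after the change.** With 20 analysed per cluster, design effect = 1 + (1.04 × 20 − 1) × 0.03 = 1.594. SE of the difference = √((0.25 + 0.21)/200 × 1.594) = 0.0605, and 0.20/0.0605 = 3.30. Power is 91.0% with a normal reference and 87.7% with t on 18 df.

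**The case against.** The strongest objection is that the article never says cluster is left out of the imputation, and never names a z-test. Chained equations can carry a multilevel imputation model, and a t reference is compatible with the stated analysis. A condensed article may leave both to an analysis plan that is not shown. This stands against the stronger reading that a reader might infer, namely that the planned imputation carries no cluster effect and the standard error is therefore too small. The documents do not support that as fact. The point survives because the article does fix the model, the imputation method and its number, and that combination in its ordinary form does not hold the stated level.

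A second objection is that the size depends on an imputation model nobody has seen. This also stands. A check with a simpler cluster-summary analysis and a z reference imputed the continuous score by arm and then dichotomised it. It assumed an auxiliary score correlated 0.7 within and 0.8 between clusters. Rejection was 7.3% with arm only, 6.8% with the auxiliary available for half of the missing patients, 5.2% with it for all, and 3.7% (conservative) with fixed cluster indicators. That check does not replicate the planned model, but it shows that the imputation part can shrink or even reverse.

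Third, the Sample size section calls 0.03 conservative, citing a median ICC of 0.01 and an interquartile range of 0 to 0.032. Results at ICC 0.05 (9.5% rejection) lie outside that range and should not be read as the expected size.

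**Conclusion.** The point holds in conditional form. At ICC 0.03, an ordinary Wald z-test on 20 clusters rejects about 7% under the null whether or not outcomes are missing. If the imputation also ignores cluster and uses arm only, rejection is about 8% and the pooled standard error is about 8% to 9% too small. About 6 points of that shortfall come from the imputation and about 3 from the few clusters. At ICC 0.01 rejection is about 6%.

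The two gaps are separate. Better imputation leaves the z-reference problem in place, and a t reference alone leaves about 6.3% under cluster-ignoring imputation at ICC 0.03.

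This rests on three assumptions: missing outcomes equal the 20% attrition, they are missing at random within arm, and the arm-only imputation model is the unfavourable case. Multilevel imputation itself was not simulated. The 5.2% for the t reference on observed data stands in for it.

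A reader might also infer that the trial is underpowered or that 10 imputations are too few. Power stays above 80%, and no calculation here bears on the number of imputations.

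**What to change.** State two things in the analysis plan, or confirm that it already states them, before any unblinded analysis.

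1. **Reference for the primary test.** Use a between-cluster t distribution: 18 df unadjusted and fewer with stratum terms (15 with three region terms, less again for the Angers initiation-time strata). Alternatively, use a permutation test over clusters that permutes only within the randomisation strata. The Nice stratum has one cluster per arm, so it allows only two arrangements.
2. **Imputation model.** Include a random cluster effect and arm, with baseline, 3- and 6-month RMDQ as predictors. These scores are already in the patient data schedule (Table 1). A random effect is preferable to fixed cluster indicators, which were conservative in the check above. The number of imputations can stay at 10 as far as this point goes.

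The cost is analysis wording, some computing time and about 3 points of power (91.0% to 87.7% with 18 df; slightly more with fewer df). No change to the number of clusters or patients is needed. At the stated trial status 41 of the planned 500 patients had been enrolled, so at that date there was ample time to settle the wording.

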### Primary objective and outcome

The primary objective is to assess the benefit of coordinated care for reducing disability, compared to usual care, in patients, aged between 18 and 60 years, consulting for subacute or recurrent acute LBP. The primary objective will be measured using the validated French version of the Roland Morris Disability Questionnaire (RMDQ) (20–22). The questionnaire comprises 24 questions and is scored from 0 (without disability) to 24 (with maximum disability). The primary outcome measure is the proportion of patients that has an improvement (lower score) of at least 4 points at 12 months after enrollment.

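### Ten imputations with 20% attrition expected: inference stays valid, but the printed primary p-value and confidence limits depend avoidably on the random seed

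*Protocol article*

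**What the plan says.** The primary outcome is binary: the "proportion of patients that has an improvement (lower score) of at least 4 points at 12 months after enrollment" on the Roland Morris questionnaire (Primary objective and outcome). For its comparison between groups the Statistics section states: "The analysis will be performed using a multilevel logistic mixed model", with the cluster as a random effect. The same section then says, for the multilevel models generally: "Missing data will be treated using a set of 10 multiple imputations based on chained equations". Testing is two-sided at 5% ("The analyses will be performed bilaterally with the alpha-risk set at 5" per cent).

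The Sample size section lists "An attrition rate of 20" per cent among its assumptions and adds that patients lost to follow-up will not be replaced. The 12-month questionnaire is completed at home (Patients' data). Beyond "a set of 10 multiple imputations", the article gives no rule for raising the number of imputations and no target for Monte Carlo error.

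**The concern.** Multiple imputation draws random values, so its pooled result changes a little from one seed to the next. Ten imputations are often defended on the efficiency of the point estimate. Efficiency does not show how stable the printed p-value and confidence limits are, and these are what readers of a trial tested at 5% will look at. With about one primary outcome in five possibly imputed, a statistician rerunning the same data under the same plan could report visibly different limits and, if the result is close to the threshold, a different verdict on significance. More imputations remove nearly all of this variation.

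**Working it through.** **Inputs from the protocol article.** 10 imputations, two-sided 5% test (Statistics). 20% attrition, 80% power, "50% of patients in the control group (Usual-care group) and 70% of those in the interventional group", mean cluster size 25, coefficient of variation of cluster size 0.2, intraclass correlation 0.03 (Sample size).

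**Assumptions, not in the document.** Attrition is read as a missing 12-month score: 0.20 × 500 = 100 patients. The fraction of missing information (FMI) is taken as 0.10 to 0.20. In simulated 20-cluster trials with 20% missing it ran from 0.09 to 0.30, mostly 0.10 to 0.20.

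**Step 1, the plan's own figure.** Two proportions, 0.5 and 0.7, at 80% power need 93 per arm, or 103 with continuity correction. The design effect is 1 + ((1 + 0.2²) × 25 − 1) × 0.03 = 1.75. Then 103 × 1.75 gives 181 after rounding up, 181 / 0.8 gives 227, and 227 / 25 = 9.08, so 10 clusters of 25 per arm and 500 patients. The stated size is reproduced.

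**Step 2, efficiency.** Relative efficiency is 1 / (1 + FMI/m). At m = 10 this is 1 / 1.01 = 99.0% for FMI 0.10 and 1 / 1.02 = 98.0% for FMI 0.20.

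**Step 3, Monte Carlo error.** As a share of the standard error it is √(FMI/m):

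- m = 10: √(0.10/10) = 10.0%; √(0.20/10) = 14.1%.
- m = 100: √(0.10/100) = 3.2%; √(0.20/100) = 4.5%.

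**Step 4, effect on the p-value.** Simulation over seeds: the pooled estimate varies with variance B/m, the between-imputation variance varies as B × χ²(m−1)/(m−1), and p comes from Rubin's degrees of freedom. The stable p is the value with unlimited imputations. The last digits carry simulation error.

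| Quantity | FMI 0.10 | FMI 0.20 |
|---|---|---|
| Stable p = 0.05, central 95% range of p, m = 10 | 0.030-0.084 | 0.023-0.108 |
| Same, m = 100 | 0.043-0.059 | 0.039-0.064 |
| Stable p = 0.064, two runs disagree, m = 10 | 24% | 34% |
| Same, m = 50 | 2% | 12% |
| Same, m = 100 | 0.2% | 3.4% |

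**Step 5, how often it matters.** The rows above are for results placed on or beside the threshold. To average over possible results, draw the stable z from a normal distribution with variance 1 and mean 1.96 + 0.84 = 2.80 (80% power) or mean 0 (no effect). Two runs then disagree on significance:

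- at 80% power, about 4% (FMI 0.10) to 6% (FMI 0.20) of the time with m = 10, and 1% to 2% with m = 100;
- under no effect, about 1.5% to 2.3% with m = 10.

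**Step 6, a result exactly as planned.** 70% versus 50% is an odds ratio of (0.7/0.3)/(0.5/0.5) = 2.33. With 250 per arm the complete-data standard error of its logarithm is √(1.75 × (1/125 + 1/125 + 1/175 + 1/75)) = 0.248. At FMI 0.20 and m = 10 the central 95% range of p over seeds is 0.0006-0.010, so the verdict does not change. The lower confidence limit runs from 1.22 to 1.47 and the upper from 3.69 to 4.48. With m = 100 these narrow to 1.32-1.39 and 3.90-4.14. At FMI 0.10 and m = 10 the limits still run 1.31-1.48 and 3.69-4.14.

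**The case against.** The strongest reply is that nothing here is wrong. Rubin's rules carry the finite number of imputations through the (1 + 1/m) term and the degrees of freedom, so the test and the interval remain valid at 10. That stands. A reader might infer an inflated type I error or poor coverage from the seed dependence. The document gives no ground for that, and none is claimed.

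Second, the large disagreement rates belong only to borderline results. That also stands, which is why the averaged figures are given beside them. A reader might take the 24-34% as the risk for this trial. At the planned power the risk is about 4-6%, and a result at the planned effect is not at risk.

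Third, 20% attrition is not an FMI of 0.20. Table 1 schedules the Roland Morris questionnaire at 3 and 6 months too, and clustering adds variance that imputation does not affect, so the FMI may well be lower. That is fair, and the FMI remains an assumption. The dependence is still visible at 0.10.

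Fourth, a statistical analysis plan may settle such details. That disposes of the seed: a reader might count its absence as a fault, but a seed is ordinary content of an analysis plan and is no part of this point. It does not dispose of the number of imputations, which the article itself states.

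**Conclusion.** The point holds as a minor improvement. The number 10 is stated and lawful, but small for the attrition that the same article expects. Under an assumed FMI of 0.10 to 0.20, with attrition read as missing 12-month scores, Monte Carlo error is 10-14% of the standard error. A stable p of 0.05 can then print roughly between 0.02 or 0.03 and 0.08 or 0.11. The chance that two runs differ on significance, averaged at the design's power, is about 4-6%, against 1-2% with 100 imputations. The planned effect would be declared significant under any realistic seed. Only its limits would shift. The simulation treats the pooled log odds ratio as approximately normal.

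**What to change.** In the Statistics section, replace 10 imputations with at least 50, and preferably 100 for the primary outcome. For a stable p of 0.064, going from 10 to 50 cuts disagreement between two runs from 24-34% to 2-12%, and 100 cuts it to 0.2-3.4%. The cost is computing time only: sample size, data collection and the analysis model are untouched.
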